## Abstract

**Background:**

Graves’ disease (GD) is characterized by thyrotoxicosis and goiter and arises through circulating autoantibodies that bind to, and stimulate, the thyroid hormone receptor (TSHR). A temporal relation between the onset of hyperthyroidism and the onset of ophthalmopathy, a common extrathyroidal manifestation, has been demonstrated. Graves’ ophthalmopathy (GO) is typically characterized by an inflammation and expansion of the extraocular muscles and an increase in retroorbital fat. There are currently three forms of therapies offered for hyperthyroidism caused by Graves’ disease: antithyroid drugs (ATD) (thionamides), radioiodine ablation (RAI) and thyroidectomy (Tx). To date, there is no clear recommendation on the treatment of Graves’ disease and GO, mainly due to the individuality of the disease in each patient. The aim of the study is to examine the difference in the outcome of GO in patients with moderate-to-severe GO who receive Tx versus further ATD after suffering their first relapse of GO, or in which GO stays the same following the initial decrease in ATD therapy after 6 months.

**Methods/Design:**

This prospective randomized clinical trial with observer-blinded analysis will analyze 60 patients with moderate-to-severe GO who receive Tx versus ATD without surgery. Main outcome variables include: muscle index measurements via ultrasound and thyroid antibody levels. Additional outcome variables include: Clinical Activity Score (CAScore), NOSPECS score, superonasal index measurements via ultrasound, and quality of life score.

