Thyroidectomy also provides definitive treatment, without exposure to radiation. Total thyroidectomy has also been shown to induce euthyroidism faster and more permanently (97%) than in patients who received RAI (73%), as well as less frequent persistence of GO, in accordance with other studies [6, 21, 22, 26, 27, 30]. In addition, levels of thyroid-stimulating immunoglobulins also rapidly and steadily declined in patients who received total thyroidectomy compared to those who underwent RAI or who took ATD [30]. Several studies have demonstrated a significant improvement of GO in patients who underwent thyroidectomy [10, 31, 32]. However, the patients who undergo thyroidectomy do need life-long substitution of thyroid hormone and have a neck scars [11]. Surgery is also associated with complications, such as permanent or transient recurrent laryngeal nerve palsy, permanent or transient hypoparathyroidism and neck hematoma requiring re-operation [33].

At present, there is no consensus on the treatment of Graves’ disease and GO, mainly due to the fact that the pathophysiology of the disease is still not completely understood, as well as the different courses of the disease in each patient. There are few published prospective randomized trials comparing the different therapies. To our knowledge, no studies have prospectively examined the effects of Tx and ATD on GO.

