## Methods/design

### Objective of the study

The overall objective of this prospective randomized clinical trial with observer-blinded analysis is to assess the outcome of GO in patients with moderate-to-severe GO who receive early Tx after their first relapse of GO or in which GO stays the same following the initial decrease in their ATD therapy after 4–6 months.

The main outcome variables investigated include: muscle index (MI) measurements via ultrasound before randomization and 1 year after the conducted therapy, as well as thyroid antibody levels, measured at each follow-up appointment. Additional outcome variables such as CAScore/NOSPECS score (calculated at each appointment), superonasal index (SNI) measurements via ultrasound and quality of life score (both obtained before randomization and 1 year after the conducted therapy) will be analyzed. See Tables 4 and 5.

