### Power calculation

The main study outcome variable will be muscle index (MI), where a difference of 1 corresponds to a difference of one clinical grade (grade II or grade III). We assume, that a proportion of patients (in both treatment groups) will not respond to their treatments. Therefore, an observed difference in MI of 0.7 is defined as clinically relevant in the study. A sample size of 29 in each group will have 90% power to detect a difference in mean changes of 0.7, making a conservative assumption about the standard deviation of the changes of 0.8, and using a two-group *t* test with a two-sided significance level of 0.05 (nQuery Advisor 7.0). At randomization patients will be stratified according to their MI grading (grade II versus grade III).

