### Statistical analysis

The data will be analyzed according to the intention-to-treat principle. This means, that for patients with missing MI values at follow-up measurements a conservative value will be imputed. If patients have a SNI >  7 during follow-up, which requires additional treatment, later MI values will be estimated using last value carried forward. The primary and continuous secondary endpoints will be analyzed using repeated measures analysis of covariance, using the randomization group as factor and the baseline values of MI as covariate. The contrast of main interest is the difference between groups in the means computed over all post-randomization measurements. MI and SNI will be obtained before randomization and 1 year after the conducted therapy. Quality of life questionnaire will also be obtained before randomization and after 1 year of follow-up. Further binary secondary endpoints will be analyzed by Mantel-Haenszel tests stratified for the clinical MI grading at baseline. All secondary endpoints will be analyzed at the specified time points (see Tables 4 and 5) and reported and thus no correction for multiple testing is done. Any analyses that will be conducted, but which are not mentioned in the study protocol, will be interpreted as explorative. A statistical analysis plan detailing all statistical computations will be completed prior to the lock of the database. Values are given as *p* values and odds ratio (95% confidence interval); *p* values < 0.05 are considered statistically significant. Analysis of data will be performed using SPSS (Statistical Package for Social Sciences, Chicago, IL, USA) v21 for Windows.

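### Thyroid antibody level is declared a main outcome beside muscle index, but only muscle index is powered and no rule says which of the two decides the trial

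*Protocol article*

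**What the plan says.** The protocol article gives two accounts of its main outcome.

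- **Two main outcomes.** Abstract, Methods/Design: "Main outcome variables include: muscle index measurements via ultrasound and thyroid antibody levels". Objective of the study: "The main outcome variables investigated include: muscle index (MI) measurements via ultrasound before randomization and 1 year after the conducted therapy", continued by "as well as thyroid antibody levels, measured at each follow-up appointment". Both places list CAScore, NOSPECS, superonasal index and quality of life separately, as additional variables.
- **One main outcome.** Power calculation: "The main study outcome variable will be muscle index (MI". That section then states "A sample size of 29 in each group will have 90% power to detect a difference in mean changes of 0.7", with a standard deviation of 0.8 and a two-sided level of 0.05. Antibody levels do not appear in it.
- **No name and no rule.** Statistical analysis refers to the primary and the continuous secondary endpoints without saying which variable is primary. It says of the secondary endpoints that they are "reported and thus no correction for multiple testing is done". It then applies the 0.05 threshold for statistical significance without distinguishing between endpoints.

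No section calls antibody levels secondary. None gives a hierarchy, a requirement that both outcomes succeed, or a split of alpha.

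**The concern.** Two sections present antibody level as equal in rank to MI, and one section excludes it. If both are main outcomes and neither is subordinate, a report could rest its main claim on whichever reaches 0.05.

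Two separate things are at stake:

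- **Error rate.** If thyroidectomy affects neither outcome, there are two chances of a false main-outcome claim instead of one.
- **Interpretation.** The stated aim is the outcome of Graves' ophthalmopathy, and antibodies are a laboratory marker. The background already reports that "levels of thyroid-stimulating immunoglobulins also rapidly and steadily declined in patients who received total thyroidectomy", in comparison with radioiodine or drug treatment. A real antibody difference is therefore foreseeable, and it could be presented as trial success while MI shows nothing.

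**Working it through.** **Step 1. Reproduce the plan's figure for MI.** Inputs from Power calculation: difference 0.7, SD 0.8, two-sided alpha 0.05, power 90%, two-group t test.

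- Standardised difference: 0.7 / 0.8 = 0.875.
- Normal approximation: n = 2 × (1.960 + 1.282)² / 0.875² = 2 × 10.51 / 0.7656 = 27.5, so 28 per group.
- Exact noncentral t: 28.44, so 29 per group, with power 90.6%.

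The stated 29 per group is correct for MI tested alone at 0.05.

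**Step 2. Does the analysis section settle which outcome is primary?** It does not settle it cleanly.

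- *For MI:* the missing-data rules concern MI, baseline MI is the covariate, and randomization is stratified by MI grade.
- *Against:* the contrast of main interest is a mean over all measurements after randomization. Table 5 has one ultrasound after treatment, at 1 year, but blood tests at all four follow-ups. On that schedule the contrast suits antibodies better than MI. (Post-treatment interventions also mentions ultrasound at 16 and 32 weeks. That conflict is a separate issue.)

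**Step 3. Error rate if either outcome may carry the claim at 0.05.** Antibodies are counted as one test.

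- Both nulls true, tests independent: 1 − 0.95² = 0.0975, or 9.75%.
- Both nulls true, tests correlated (bivariate normal). The document gives no correlation, so these are assumed values:

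| Correlation | At least one false claim |
|---|---|
| 0 | 9.75% |
| 0.3 | 9.5% |
| 0.5 | 9.1% |
| 0.7 | 8.3% |
| 0.9 | 7.0% |

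- Antibody null false: only MI can be falsely rejected, at 5%. The problem is then one of interpretation, not of type I error.

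**Step 4. What keeping two main outcomes would cost.** With alpha split equally (0.025 each):

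- Normal approximation for MI: 2 × (2.241 + 1.282)² / 0.7656 = 32.4, so 33 per group.
- Exact t: 33.71, so 34 per group, 68 in total against the 60 planned.
- MI power at 0.025 is 84.5% with 29 per group and 85.8% with 30.
- Antibody power cannot be computed, because no effect or SD is given.

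**Step 5. With MI as sole primary.** Alpha stays at 0.05 and Step 1 stands unchanged.

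**The case against.** The strongest reply is that the operative sections point to MI alone. The power calculation uses the singular, and the relevant difference, SD, stratification, covariate and missing-data rules all belong to MI. On this view the phrase in the abstract and the objectives is loose summary language. That is the better reading of what was intended, and the fix adopts it. It does not remove the contradiction: the two-outcome statement appears twice, each time set apart from the additional variables, and nothing demotes antibodies.

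A second reply is that the analysis plan, due before database lock, can set the testing rules. It can supply detail, but the protocol's own statements of what is primary must agree. Masking is described only for the ophthalmologist who makes the follow-up measurements, so a choice left until shortly before lock could be made when antibody results by arm are known.

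Several stronger readings are tempting, and the document does not support them:

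- *Multiplicity between the two main outcomes is waived.* The no-correction sentence is about secondary endpoints. For two main outcomes the document is silent. Either way antibodies are tested at an uncorrected 0.05.
- *The secondary endpoints alone inflate error seriously.* Table 5 gives 8 tests (CAScore 3, NOSPECS 3, superonasal index 1, quality of life 1), and 1 − 0.95⁸ = 34%. With antibodies at four visits there are 12 tests, and 1 − 0.95¹² = 46%. Both figures treat repeated measurements in the same patients as independent, which is implausible. Leaving secondary endpoints uncorrected beside one powered primary is also common practice.
- *The trial is underpowered.* The 84.5% and 85.8% apply only to an alpha split that the plan does not propose.

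**Conclusion.** The point holds as an inconsistency in the status of antibody levels, with no rule to resolve it. If either outcome may carry the claim, the familywise error is at most 9.75%, and 7.0% to 9.5% for assumed correlations of 0.9 to 0.3. These figures require both nulls to be true. They cannot be combined with the expectation that antibodies will differ; in that case the exposure is a laboratory result read as benefit to the eyes.

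A reader might infer that the trial plans to claim success on antibodies, or that its type I error is uncontrolled in general. No section says the first: such a claim is left open, not planned. The second is too broad, because with MI as sole primary the confirmatory error is 5%. The sample size is not at fault. Because the ambiguity bears on what a phase III trial may conclude, it should be resolved in the protocol text.

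**What to change.** 1. In the abstract and in Objective of the study, name MI as the sole primary outcome, in agreement with Power calculation, and list thyroid antibody levels with the secondary outcomes.
2. In Statistical analysis, name MI as the primary endpoint.
3. In the same section, replace the reasoning that reporting all secondary endpoints makes correction unnecessary. Suggested wording: *Secondary endpoints are reported as estimates with 95% confidence intervals and nominal p values; the confirmatory conclusion rests on the primary MI test only.*

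The change should not fix a time point for MI in the abstract or objectives alone. Adding 1 year there would conflict with the contrast over all measurements after randomization in Statistical analysis. The MI time point or contrast must be worded consistently with that section, and is a separate matter.

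The cost is wording only. The 29 per group, the two-sided 0.05 level and the 90% power for MI all stand. The downside is that antibody results can no longer be presented as confirmatory, although the trial gives no power justification for such a claim. If both outcomes are to stay primary, the protocol would need a stated rule (hierarchy, both required, or split alpha) and a power justification for each. With an equal split of alpha, that means at least 34 per group for 90% power on MI.

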**Discussion:**

This study should allow for better therapeutic choices in patients with moderate-to-severe GO. In addition, it should demonstrate whether the outcome of GO in patients with moderate-to-severe GO is better in those who receive early Tx versus further ATD. Furthermore, this study will aim to establish a standard glucocorticoid scheme before and after Tx in patients with moderate-to-severe EO.

**Trial registration:**

Eudra-CT: 2015–003515-38; Medical University of Vienna Protocol Record 1839/2015.

Date of Ethics Committee approval: 19 January 2017.

Registered on 27 January 2017.

**Electronic supplementary material:**

The online version of this article (10.1186/s13063-018-2876-0) contains supplementary material, which is available to authorized users.

## Background

### Medical problem

Graves’ disease is characterized by thyrotoxicosis and goiter and arises through circulating autoantibodies that bind to, and stimulate, the thyroid hormone receptor (TSHR) [1]. The annual incidence lies at 14 per 100,000 [2] and it is more frequent in women, with a ratio of approximately 4–6:1 [3]. The disease can also cause extrathyroidal manifestations, the most common one being ophthalmopathy [1].

Graves’ ophthalmopathy (GO) is typically characterized by an inflammation and expansion of the extraocular muscles and an increase in retroorbital fat [4]. The interaction between orbital fibroblasts and CD4+ lymphocytes has led researchers to believe that corticosteroids can be used as a standard therapy to suppress this immune reaction [5]. Swelling and enlargement of the orbital tissues can result in an increase in intraorbital pressure causing exophthalmos and venous engorgement. The different stages of GO are classified according to the European Group on Graves’ Orbitopathy (EUGOGO) [6]: mild, moderate to severe and sight-threatening.

The Clinical Activity Score (CAScore) has been previouly  published by Mourits et al. [7]. A CAScore of ≥ 3/7 indicates active disease [6] and a score of 4 or higher has an 80% positive predictive value and 64% negative predictive value in the response of patients to corticosteroid therapy. Another classification, No signs/symptoms, Only signs/no symptoms, Soft tissue involvement, Proptosis, Extraocular muscle involvement, Corneal involvement, Sight loss (NOSPECS), was first described by Werner in 1977 [8].

Risk factors associated with the development of GO include gender (female to male ratio: 2:1), cigarette smoking (also associated with relapse after therapy with antithyroid drugs (ATD) and deterioration of GO following radioablation therapy (RAI)), severity of hyperthyroidism and the degree of autoimmunity [9].

The best treatment should offer fast relief of clinical symptoms by eradicating the cause of thyrotoxicosis with only minimal risk for the patient [10]. Patients with moderate-to-severe and active GO preferably receive intravenously administered glucocorticoids as first-line therapy. If this does not work, second-line therapy includes a second course of high-dose intravenously administered glucocorticoids, orally administered glucocorticoids in combination with cyclosporine and possibly orbital radiotherapy [6, 11]. In terms of the dosages and length of glucocorticoid therapy, there have been few studies published to date. A study by Bartalena et al. suggested a starting dose of 80–100 mg with a gradual tapering and withdrawal over 5–6 months in oral glucocorticoid therapy [12]. Regarding intravenously administered glucocorticoid therapy, two studies delivered 15 mg/kg for the first four infusions followed by 7.5 mg/kg for the remaining eight infusions for a total of 12 infusions over 10 weeks [13, 14]. However, there is currently no consensus on the dosage or therapy length of either orally or intravenously administered glucocorticoid therapy.

The three types of therapies offered for Graves’ disease are ATD, RAI and total thyroidectomy (Tx). ATD therapy is generally well-tolerated, carries a low risk of hypothyroidism, carries no need of radiation exposure and is relatively safe to use in pregnancy and breastfeeding. However, it should only be given for a limited period of time (between 18 and 24 months) due to the side-effects, such as hepatitis and agranulocytosis, as well as a high relapse rate of up to 50% following withdrawal of the therapy [2, 15–19].

Definitive thyroid tissue ablation by RAI leads to lifelong hypothyroidism in up to 80% of patients. However, the patients are exposed to radiation which can cause a worsening of GO (radiation thyroiditis) due to a massive efflux of thyroid antigens from the thyroid that then stimulate antithyroid antibody production [19–27]. An exacerbation of preexisting ophthalmopathy can be prevented with therapy using orally administered glucocorticoids after RAI for anywhere between 6 and 12 weeks [6, 28, 29].

Thyroidectomy also provides definitive treatment, without exposure to radiation. Total thyroidectomy has also been shown to induce euthyroidism faster and more permanently (97%) than in patients who received RAI (73%), as well as less frequent persistence of GO, in accordance with other studies [6, 21, 22, 26, 27, 30]. In addition, levels of thyroid-stimulating immunoglobulins also rapidly and steadily declined in patients who received total thyroidectomy compared to those who underwent RAI or who took ATD [30]. Several studies have demonstrated a significant improvement of GO in patients who underwent thyroidectomy [10, 31, 32]. However, the patients who undergo thyroidectomy do need life-long substitution of thyroid hormone and have a neck scars [11]. Surgery is also associated with complications, such as permanent or transient recurrent laryngeal nerve palsy, permanent or transient hypoparathyroidism and neck hematoma requiring re-operation [33].

At present, there is no consensus on the treatment of Graves’ disease and GO, mainly due to the fact that the pathophysiology of the disease is still not completely understood, as well as the different courses of the disease in each patient. There are few published prospective randomized trials comparing the different therapies. To our knowledge, no studies have prospectively examined the effects of Tx and ATD on GO.

### Aim of the study

The aim of this study is to assess the outcome of GO in patients with moderate-to-severe GO who receive early Tx after their first relapse of GO or in which GO stays the same following the initial decrease in their ATD therapy after 4–6 months. Furthermore, this study will aim to establish a standard glucocorticoid scheme before and after Tx. Patients will undergo follow-up examinations for 1 year after study inclusion. The data acquired from this study will allow for better therapeutic choices in patients with GO. This study is considered a phase III study.

## Methods/design

### Objective of the study

The overall objective of this prospective randomized clinical trial with observer-blinded analysis is to assess the outcome of GO in patients with moderate-to-severe GO who receive early Tx after their first relapse of GO or in which GO stays the same following the initial decrease in their ATD therapy after 4–6 months.

The main outcome variables investigated include: muscle index (MI) measurements via ultrasound before randomization and 1 year after the conducted therapy, as well as thyroid antibody levels, measured at each follow-up appointment. Additional outcome variables such as CAScore/NOSPECS score (calculated at each appointment), superonasal index (SNI) measurements via ultrasound and quality of life score (both obtained before randomization and 1 year after the conducted therapy) will be analyzed. See Tables 4 and 5.

### Trial population

Sixty patients with moderate-to-severe GO who suffer their first relapse of GO or in which GO stays the same following the initial decrease in their ATD therapy after 4–6 months will be included.

### Clinical sites

The clinical sites included in this study are the Department of General Surgery, the Department of Endocrinology and Metabolism, the Department of Ophthalmology and the Department of Nuclear Medicine, Vienna General Hospital (academic hospital), Medical University Vienna. In order to ensure adequate participant enrollment, all clinical sites will work together meticulously. In addition, the clinical trial will be presented at other departments of surgery, endocrinology and nuclear medicine within Austria and at medical conferences to aid in achieving adequate participant enrollment. All departments will be involved in enrolling the participants. The intervention allocation will be conducted at the Department of Surgery through the Randomizer for Clinical Trials (see page 12).

